### Participant timeline and study flowchart

The participant timeline and study flowchart are presented in Figs. 4 and 5, respectively. A filled Standard Protocol Items: Recommendations for Interventional Trials (SPIRIT) Checklist is available (see Additional file 1).

**Fig. 4 Fig4:**
[figure not shown]
The Standard Protocol Items: Recommendations for Interventional Trials (SPIRIT) participant timeline in the POCKET trial. ROTEM®, rotational thromboelastometry

**Fig. 5 Fig5:**
[figure not shown]
Study flowchart of the POCKET trial

### Recruitment

Patients will be recruited in the two mixed medical-surgical ICUs of Hospital Israelita Albert Einstein in São Paulo, Brazil. On a daily basis, the research team will actively search the records and patient list for patients admitted with a diagnosis of cirrhosis. Additionally, on-call and horizontal care staff will be encouraged to recommend eligible patients to the research team at any time. The current recruitment rate is four patients per month with an expected duration of recruitment of 42 months. Recruitment rate will be monitored trimonthly.

### Randomization, allocation and blinding

Allocation sequence with random numbers will be computer-generated using random, varied size blocks and stratification by severe renal failure (i.e., hemodialysis program). The randomization sequence will be stored in individually separated and sequentially numbered opaque, sealed envelopes and kept secured in a locker with restricted access (centralized at ICU pharmacy). After the consent term is signed and coagulation tests collected, patients will be randomly assigned to study groups with an allocation ratio of 1:1:1.

Allocation concealment will be preserved by holding randomization sequence disclosure until the consent term is signed and coagulation tests collected. Patients will be enrolled by an on-call recruiter, and assignment to intervention will be provided by an independent researcher, who will be the only one to know which intervention the patient will be assigned to. The research subjects, central venous catheter inserter and outcome assessors will be blinded to the assigned intervention and bleeding will be assessed by the use of the HEME tool [41] immediately after CVC and 24 h after the procedure. The catheter inserter is not directly responsible for care of the patient included in the trial and will not have access to the patient’s chart. In case of major bleeding or serious transfusion-related adverse reaction, unblinding to the attending physician is anticipated.

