### Sample size calculation

We calculated the sample size based on the primary efficacy endpoint. We assumed a transfusion rate of 90% in the Coagulogram-based group (i.e., control group) [11] and an absolute risk reduction of 25% for the Thromboelastometry-based and Restrictive groups. Using a study power of 0.80 and alpha of 0.05, we need *n* = 43 patients per group. The sample size was adjusted for multiple comparisons (additional increase of 20%, *n* = 8 per group) (Coagulogram-based versus Thromboelastometry-based, Coagulogram-based versus Restrictive, and Thromboelastometry-based versus Restrictive) according to Witte et al. [43]. To account for loss to follow-up, we have added 10% (*n* = 4) more patients to the adjusted sample size. The final required sample will be 55 patients per group (total estimated sample size of 165 patients).

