### Statistical analysis plan

All analyses will be performed as intention-to-treat. Categorical variables will be summarized as absolute and relative frequencies. Normality will be tested with the Kolmogorov-Smirnov test. Accordingly, continuous variables with normal distribution will be summarized as mean ± SD, or median and interquartile range (IQR) in case of non-normal distribution.

Comparisons between groups of continuous variables will be performed with one-way analysis of variance (one-way ANOVA) followed by Tukey’s test for multiple comparisons (for normally distributed variables), or the Kruskal-Wallis test followed by the Mann-Whitney *U* test (for non-normally distributed variables). Proportions between groups will be analyzed with the chi-square test or Fisher’s exact test, as appropriate.

All binary outcomes will be analyzed using a generalized linear model with binomial distribution and logit link function followed by pairwise comparisons adjusted by Bonferroni correction for multiple comparisons. Pairwise comparisons will be presented as odds ratio (OR) along with 95% confidence interval (95% CI), which will be calculated by logistic regression.

A survival curve will be performed with the Kaplan-Meier estimator and the log-rank test will be used to compare groups. To assess time-to-event (28-day mortality), an unadjusted Cox proportional hazards regression model will be performed. The hazard ratio (HR) with its respective 95% CI will be reported.

Prespecified subgroup analysis for the primary outcome will be presented as a Forest plot, and will include the presence of hypothermia (<35 °C), SAPS 3 score (≥50 points) and MELD score (≥25 points). Interaction between groups and each covariate will be assessed by multivariate logistic regression.

Two-tailed tests will be used and when *p* < 0.05, the test will be considered statistically significant. To account for multiple comparisons (Coagulogram-based versus Thromboelastometry-based, Coagulogram-based versus Restrictive and Thromboelastometry-based versus Restrictive), the α level will be adjusted to 0.0167.

We will make maximum effort to reduce missing data. We will use the multiple imputation method to handle missing data when necessary. The Statistical Package for the Social Sciences version 22.0 (IBM Inc., Chicago, IL, USA) will be used for statistical analyses. GraphPad Prism version 6.07 (GraphPad Software Inc., La Jolla, CA, USA) will be used for graph plotting.

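### Randomization is stratified by hemodialysis, but no planned analysis uses the stratum; if dialysis predicts the outcome, the tests are somewhat conservative

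*Protocol article*

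**What the plan says.** In the protocol article, section Randomization, allocation and blinding, the sequence uses random blocks of varying size with "stratification by severe renal failure (i.e., hemodialysis program", and "patients will be randomly assigned to study groups with an allocation ratio of 1:1:1". No other stratification factor is named, and no reason is given for this one.

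The section Statistical analysis plan sets out the methods:

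- **Binary outcomes:** "All binary outcomes will be analyzed using a generalized linear model with binomial distribution and logit link function", followed by Bonferroni-adjusted pairwise comparisons reported as odds ratios.
- **Proportions:** chi-square or Fisher's exact test.
- **Continuous outcomes:** one-way ANOVA with Tukey's test, or Kruskal-Wallis followed by Mann-Whitney.
- **28-day mortality:** Kaplan-Meier curves, the log-rank test, and "an unadjusted Cox proportional hazards regression model will be performed".
- **Subgroups and interactions:** hypothermia, SAPS 3 and MELD.

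Hemodialysis appears in none of these.

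**The concern.** Stratified blocks hold the dialysis mix nearly equal across arms, so variation between dialysis strata largely drops out of the comparison of arms. A test that ignores the stratum still counts that variation in its standard error. If the stratum is prognostic, the standard error is too large, the actual type I error falls below its nominal level, and some power is given up. An analysis would normally reflect the restriction in the randomization. Fixing this in advance also removes later discretion over whether adjusted or unadjusted results are reported. What is at stake is efficiency, not protection against false positives.

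**Working it through.** **Inputs from the article.** Sample size calculation: "We assumed a transfusion rate of 90% in the Coagulogram-based group", "an absolute risk reduction of 25% for the Thromboelastometry-based and Restrictive groups" (so 90% versus 65%), and "Using a study power of 0.80 and alpha of 0.05". Statistical analysis plan: "Two-tailed tests will be used", and 0.0167 for each pairwise comparison.

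**Assumptions, because the article gives no figures.** Dialysis share 20%, 35% or 50%. Odds ratio (OR) of dialysis for transfusion 1, 2, 3, 5 or 10, equal in both arms. Perfect balance within strata. No interim looks. 51 evaluable per arm, which is 43 + 8 before the allowance for loss.

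**Step 1: the article's own figure.** With the pooled two-proportion formula and mean rate (0.90 + 0.65)/2 = 0.775:

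n = [1.960 √(2 × 0.775 × 0.225) + 0.842 √(0.90 × 0.10 + 0.65 × 0.35)]² / 0.25² = 42.6, so 43 per group.

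This matches. Then 43 + 8 + 4 = 55, and 3 × 55 = 165.

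**Step 2: how much variance the stratum removes.** For each arm, average p(1 - p) within strata, sum over the two arms, and divide by the unstratified sum 0.09 + 0.2275 = 0.3175. Example with OR 5 and a 50% share: the stratum rates that average to 90% and 65% are 0.9626 (dialysis) and 0.8374 (no dialysis) in control, and 0.8212 and 0.4788 in the new arm.

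- Control: 0.5 × 0.9626 × 0.0374 + 0.5 × 0.8374 × 0.1626 = 0.0861.
- New arm: 0.5 × 0.8212 × 0.1788 + 0.5 × 0.4788 × 0.5212 = 0.1982.
- Ratio: (0.0861 + 0.1982)/0.3175 = 0.895.

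The ratio is 1 at OR 1 and 0.978 at OR 2 with the same share. A weak stratum leaves almost nothing to recover.

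**Step 3: power.** One pairwise comparison, 200,000 simulated trials per cell, two-sided alpha 0.0167. Each cell shows the plain chi-square test, then the Cochran-Mantel-Haenszel test without continuity correction.

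| OR of dialysis | 20% share | 35% share | 50% share |
|---|---|---|---|
| 1 | 76.8% / 75.7% | 76.6% / 75.7% | 76.8% / 75.8% |
| 2 | 76.9% / 76.3% | 76.9% / 76.9% | 76.9% / 76.8% |
| 3 | 77.1% / 77.1% | 77.1% / 78.0% | 77.0% / 78.1% |
| 5 | 77.4% / 78.1% | 77.4% / 79.2% | 77.5% / 80.2% |
| 10 | 77.7% / 79.0% | 77.9% / 81.1% | 77.9% / 83.1% |

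The change is about -1 point at OR 1, -0.6 to 0.0 at OR 2, 0.0 to +1.1 at OR 3, +0.7 to +2.7 at OR 5, and +1.4 to +5.2 at OR 10.

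**Step 4: type I error of the plain chi-square test (nominal 0.0167).**

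- Common rate 90%, the assumed control rate: 0.0167 down to 0.0129 across all cells.
- Common rate 65%: 0.0169 to 0.0175 at OR 1, 0.0107 to 0.0141 at OR 5, and 0.0066 to 0.0132 at OR 10.

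The Cochran-Mantel-Haenszel test lies between 0.0138 and 0.0170 throughout. The values slightly above 0.0167 at OR 1 reflect the chi-square approximation and simulation error; with no stratum effect, they cannot come from omitting the stratum.

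**Step 5: what happens to the odds ratio.** In the Step 2 example the odds ratio for transfusion, control versus new arm, is (0.90/0.10)/(0.65/0.35) = 4.85 overall. Within the dialysis stratum it is (0.9626/0.0374)/(0.8212/0.1788) = 5.60, and it is the same without dialysis. Adjustment therefore changes the quantity reported as well as its precision.

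**The case against.** The strongest reply is that nothing in the article ties dialysis to the primary endpoint. Pre-procedure transfusion follows from INR, aPTT, platelets and fibrinogen in the control arm, from thromboelastometry values in the second, and from INR and platelets in the third; none is a renal criterion. A reader might infer that dialysis was chosen as a prognostic factor, and hence that the planned tests definitely lose power. The article does not support this. It gives no reason for the choice, and at an OR of 2 or less there is nothing to gain. This part of the reply stands.

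A reader might also infer that the primary model is fixed as unadjusted. It is not: the article names the logit model without listing covariates, and a fuller plan may add the stratum. Only the Cox model is called unadjusted. The plain chi-square and log-rank tests as described, however, carry no stratum.

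A third tempting reading is that the stated error rate is wrong in a harmful way. An actual error below the nominal level poses no false-positive risk. The lowest values need both a common rate near 65% and a very strong stratum effect; at 90% the error stays between 0.0129 and 0.0167.

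Finally, the trial's power at 0.0167 is a separate matter. The Step 1 formula with alpha 0.0167 gives 58 per group before dropout, and about 75% power with 51. That shortfall comes from sizing at 0.05 and not from the stratum.

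What remains is that the one factor built into the randomization is absent from every named analysis, and is expressly left out of one.

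**Conclusion.** The point holds as a modest, conditional matter of efficiency. The mismatch between stratified randomization and the named analyses is on the page. For the primary comparison, including the stratum is worth 0 to about 3 points of power at a dialysis OR of 3 to 5. It is worth nothing, or a loss of up to about 1 point, at an OR up to 2. About 5 points is reached only at OR 10 with half the patients on dialysis. These figures rest on assumed shares and odds ratios, 51 evaluable per arm, balanced strata and a single analysis. The effect on the 28-day mortality analysis was not quantified, as the article gives no event rates. Validity is not threatened.

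**What to change.** State in the analysis plan, before unblinding, that:

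- the logistic model for the primary efficacy endpoint, and the ANOVA models, include the hemodialysis stratum used at randomization as a covariate;
- the Cochran-Mantel-Haenszel test replaces the plain chi-square test;
- the log-rank test and the Cox model for 28-day mortality are stratified by hemodialysis;
- the unadjusted results are kept as sensitivity analyses;
- the adjusted odds ratio is conditional on the stratum and differs in meaning from the unadjusted one.

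The Kruskal-Wallis and Mann-Whitney route takes no covariate, so the plan should say whether it stays unadjusted or uses a stratified rank test.

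The cost is a few sentences and no new data, since the stratum must be known to randomize. The statistical price is up to about 1 point of power if dialysis proves not to be prognostic.

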### Sample size calculation

We calculated the sample size based on the primary efficacy endpoint. We assumed a transfusion rate of 90% in the Coagulogram-based group (i.e., control group) [11] and an absolute risk reduction of 25% for the Thromboelastometry-based and Restrictive groups. Using a study power of 0.80 and alpha of 0.05, we need *n* = 43 patients per group. The sample size was adjusted for multiple comparisons (additional increase of 20%, *n* = 8 per group) (Coagulogram-based versus Thromboelastometry-based, Coagulogram-based versus Restrictive, and Thromboelastometry-based versus Restrictive) according to Witte et al. [43]. To account for loss to follow-up, we have added 10% (*n* = 4) more patients to the adjusted sample size. The final required sample will be 55 patients per group (total estimated sample size of 165 patients).

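### The 20% sample-size increase does not match the three comparisons at α 0.0167 that the plan will test; per-comparison power against control is about 0.73 to 0.78, not the stated 0.80

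*Protocol article*

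**What the plan says.** Under Sample size calculation, the protocol article builds its number in three steps.

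- **Base.** "We assumed a transfusion rate of 90% in the Coagulogram-based group (i.e., control group") and "an absolute risk reduction of 25% for the Thromboelastometry-based and Restrictive groups", so 65% in both new arms. "Using a study power of 0.80 and alpha of 0.05", it needs 43 per group.
- **Multiplicity.** "The sample size was adjusted for multiple comparisons (additional increase of 20"%, n = 8 per group, which makes 51. The text names the comparisons covered: Coagulogram-based versus Thromboelastometry-based, Coagulogram-based versus Restrictive, and Thromboelastometry-based versus Restrictive. It cites a published method (reference 43).
- **Loss.** A further 10%, given as n = 4 and described as added to the adjusted number. "The final required sample will be 55 patients per group", 165 in total.

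Under Statistical analysis plan, tests are two-tailed, binary outcomes go through a logistic model with Bonferroni-corrected pairwise comparisons, and for the same three comparisons "the α level will be adjusted to 0.0167".

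**The concern.** The sizing and the analysis claim to serve the same family of three tests, but they do not use the same significance level. Lowering α from 0.05 to 0.0167 at fixed power costs a fixed proportion of extra patients, and that proportion is not 20%. If the increase is too small, the power of 0.80 claimed for the primary efficacy endpoint is not available at the threshold that will decide the result. A non-significant comparison with control would then be somewhat more likely than the protocol tells its readers.

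**Working it through.** **Inputs (all from the protocol article).** p₁ = 0.90, p₂ = 0.90 − 0.25 = 0.65, power 0.80, base α 0.05 and base n 43 (Sample size calculation); two-sided tests and α 0.0167 per comparison (Statistical analysis plan); 1:1:1 allocation (Randomization, allocation and blinding).

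**Formula.** Pooled two-proportion normal approximation, no continuity correction:

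n = [z(α/2)·√(2p̄q̄) + z(power)·√(p₁q₁ + p₂q₂)]² / (p₁ − p₂)²

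with p̄ = 0.775, √(2 × 0.775 × 0.225) = 0.5906, √(0.0900 + 0.2275) = 0.5635, z(power) = 0.842 and (p₁ − p₂)² = 0.0625.

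**Step 1: reproduce the plan's figure.** At α 0.05, z = 1.960: (1.960 × 0.5906 + 0.842 × 0.5635)² / 0.0625 = 42.6, so 43. This matches exactly.

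**Step 2: same formula at the lower levels.** The last column is the simple factor (z(α/2) + 0.842)² / (1.960 + 0.842)².

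| α per test | z | n per group | simple factor |
|---|---|---|---|
| 0.05 | 1.960 | 42.6 → 43 | 1.00 |
| 0.025 (0.05/2) | 2.241 | 51.7 → 52 | 1.21 |
| 0.0167 (0.05/3) | 2.393 | 57.0 → 58 | 1.33 |

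The planned 51 falls one short of the α 0.025 row and seven short of the α 0.0167 row. With 10% loss, 58 / 0.90 = 64.4, so 65 per group (195 in total) against the planned 55 (165).

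**Step 3: power against control at α 0.0167.**

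Power = Φ{[0.25·√n − 2.393 × 0.5906] / 0.5635}

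- n = 49.5 (55 less 10%): 0.730
- n = 51: 0.745
- n = 55 (nobody lost): 0.783

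**Step 4: does the choice of test change this?** Exact enumeration for 90% versus 65% at α 0.0167:

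| Test | 51 per group | 55 per group |
|---|---|---|
| Fisher's exact | 0.695 | 0.730 |
| Wald, logistic model | 0.722 | 0.770 |
| Pearson chi-square | 0.768 | 0.795 |
| Likelihood ratio | 0.775 | 0.816 |

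Only the likelihood-ratio test with all 55 analysed passes 0.80. None of these figures includes the cost of the two Lan-DeMets interim looks.

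**Step 5: the third comparison.** Both new arms are assumed at 65%, so no difference is specified for Thromboelastometry-based versus Restrictive. Under the planning rates that test rejects with probability of about 0.017, which is its α, yet it takes one third of the overall 0.05.

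**Step 6: the add-ons (minor).** 20% of 43 is 8.6, and 8 were added. 10% of the adjusted 51 is 5.1, and 4 were added; 10% of the unadjusted 43 is 4.3. The second does not match its own description. Together they amount to one or two patients per group.

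**The case against.** **Loss may be small.** The primary efficacy endpoint is transfusion before catheterization, decided soon after randomization and analysed by intention-to-treat. Loss to follow-up can hardly remove it, although withdrawal or refused deferred consent could remove a few patients. This stands: the realistic number analysed may be near 55, where the pooled formula gives 0.78 and chi-square 0.795. It narrows the gap only because the loss allowance fills in for the multiplicity allowance, which is not what the sample-size section says.

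**Power for at least one success is higher.** The hypothesis is worded with and/or. Simulated chi-square power to show at least one of the two reductions at α 0.0167 is about 0.90 with 51 per group and 0.91 with 55. The section does not say which power it means. However, 43 is a two-group calculation for one comparison, so 0.80 is naturally read as per-comparison power.

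**The cited method may justify 20%.** That source is not available here. Whatever it says, the analysis section fixes 0.0167, and power at that level follows from the stated inputs. A reader might infer that the authors sized for two comparisons by mistake. The documents do not support that: the text names three, and the match with α 0.025 is only numerical.

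**The third comparison is not an error.** This is correct. The protocol claims no effect for it, and a three-way Bonferroni correction is valid, if conservative. The point is only that it is not powered and that its share of α lowers the power of the other two.

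**Conclusion.** The inconsistency is real. An increase said to cover three comparisons is too small for the level at which those three will be tested: about one third is needed, not 20%. Under the planning rates, per-comparison power against control is about 0.73 to 0.75 with the 49.5 to 51 evaluable per group that the plan budgets, and about 0.78 if all 55 are analysed (pooled formula). Across the tests in the working, the range for 51 to 55 per group is 0.70 to 0.82, before any cost of the interim looks.

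A reader might infer that 0.80 is badly missed in every case, or that the trial's conclusions are compromised. Neither follows. With complete data and a chi-square or likelihood-ratio test, power is close to 0.80. Type I error control and the validity of the estimates are not touched, and the 90% and 25-point inputs are themselves round assumptions. The power statement is wrong as written, by a moderate amount.

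**What to change.** **Restate the power.** Keep 165 patients. In Sample size calculation, say that per-comparison power against control is about 0.73 to 0.78 at α 0.0167, and give the test and the evaluable number behind the figure chosen. Say that Thromboelastometry-based versus Restrictive has no assumed difference and is not powered. Correct the loss add-on so that its description and its number agree. The cost is a few sentences and a less favourable stated figure.

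**Optional, and only by an amendment made blind to interim results:**

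- Make Thromboelastometry-based versus Restrictive secondary and test the two control comparisons at α 0.025. Power is 0.79 with 51 per group and 0.83 with 55 (pooled formula).
- Or use the closed test for three groups: a global test at 0.05, then each pair at 0.05. Simulated per-pair power against control is about 0.83 to 0.85 with 49 to 51 per group, before interim boundaries.

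Neither option is free. Both relax the primary significance rule in a running trial. Recruitment began in September 2014 and the article appeared in February 2017. At four patients per month, if that rate held, about 29 × 4 = 116 patients would have been enrolled, past both planned interim looks at 55 and 110. If blindness to those results cannot be shown, only the restatement should be made.

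### The 20% added for multiplicity is about what two comparisons need; at the planned α of 0.0167 for three, 51 per group gives power of about 0.75, not 0.80

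*Protocol article*

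**What the plan says.** Under Sample size calculation, the article starts from the primary efficacy endpoint: "We assumed a transfusion rate of 90% in the Coagulogram-based group", with "an absolute risk reduction of 25% for the Thromboelastometry-based and Restrictive groups". The base calculation is made "Using a study power of 0.80 and alpha of 0.05" and gives 43 per group. Then "The sample size was adjusted for multiple comparisons (additional increase of 20" per cent, stated as 8 per group. The comparisons that this is meant to cover are listed as "Coagulogram-based versus Thromboelastometry-based, Coagulogram-based versus Restrictive, and Thromboelastometry-based versus Restrictive". A further 4 per group for loss to follow-up brings the total to 55 per group, or 165 patients.

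Under Statistical analysis plan, binary outcomes are analysed with a logit-link binomial model followed by "pairwise comparisons adjusted by Bonferroni correction for multiple comparisons". Tests are two-tailed. For the same three comparisons, "the α level will be adjusted to 0.0167".

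**The concern.** An inflation for multiple comparisons should keep the stated power once the stricter significance level is applied. The article gives both the inflation and the level, so they can be checked against each other. Dividing 0.05 by three should cost clearly more than 20% in sample size at 80% power. If it does, the quoted power of 0.80 does not apply to the tests that will be run.

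This concerns the two comparisons with the Coagulogram-based group on which the trial was sized. A non-significant result, for example for thromboelastometry, would be taken as evidence from an adequately powered test when the risk of missing the planned effect is higher than stated.

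**Working it through.** **Inputs.** From Sample size calculation: p₁ = 0.90, p₂ = 0.90 − 0.25 = 0.65, power 0.80, base α 0.05, 43 + 8 = 51 per group, 51 + 4 = 55 per group. From Statistical analysis plan: two-tailed tests, three pairwise comparisons, α 0.0167 each. Allocation is 1:1:1.

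**Formula.** Two proportions, pooled variance under the null, no continuity correction:

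n per group = [z(1−α/2)·√(2p̄(1−p̄)) + z(0.80)·√(p₁(1−p₁) + p₂(1−p₂))]² / (p₁−p₂)²

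- p̄ = 0.775, so √(2 × 0.775 × 0.225) = 0.5906
- √(0.0900 + 0.2275) = 0.5635
- z(0.80) = 0.8416, so the second term is 0.8416 × 0.5635 = 0.4742
- (p₁−p₂)² = 0.0625

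**Step 1: reproduce the plan's figure.** At α 0.05, z = 1.9600 and n = (1.1575 + 0.4742)² / 0.0625 = 42.6, so 43. This matches. The unpooled formula gives 40, the arcsine formula 41 and the continuity-corrected formula 51, so the pooled formula is the one that reproduces the plan.

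**Step 2: same formula at the adjusted levels.**

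| Comparisons | α per test | z | n (formula) | n (rounded up) | Ratio to 42.6 |
|---|---|---|---|---|---|
| 1 | 0.05 | 1.960 | 42.6 | 43 | 1.00 |
| 2 | 0.025 | 2.241 | 51.7 | 52 | 1.21 |
| 3 | 0.0167 | 2.393 | 57.0 | 58 | 1.34 |

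A 20% increase is therefore close to the Bonferroni cost of two comparisons and well below that of three. It was also rounded down: 20% of 43 is 8.6, and 8 were added. The unrounded requirement for three comparisons is 57.006, so 57 per group is enough in practice (power 0.7999). The shortfall from 51 is 6 to 7 per group.

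**Step 3: power at the plan's numbers.** Power = Φ{[0.25·√n − z(1−α/2) × 0.5906] / 0.5635}.

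- n = 51, α 0.0167: (1.7854 − 1.4133) / 0.5635 = 0.660, so power is 0.745
- n = 55, α 0.0167: (1.8540 − 1.4133) / 0.5635 = 0.782, so power is 0.783
- n = 51, α 0.025: power is 0.794

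At 51 per group the design almost meets its target for two comparisons and is about 5.5 points short for three.

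**Step 4: exact check.** Enumerating all binomial outcomes at 0.90 v 0.65 and α 0.0167 gives:

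| Test | 51 per group | 55 per group |
|---|---|---|
| Pearson chi-square | 0.77 | 0.79 |
| Likelihood ratio | 0.78 | 0.82 |
| Logistic Wald | 0.72 | 0.77 |
| Fisher | 0.70 | 0.73 |

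**Step 5: detectable effect.** With 51 per group and α 0.0167, power of 0.80 is reached for a reduction of about 27 points (90% v about 63%).

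**The case against.** The strongest objection is that 51 is too pessimistic. The primary efficacy endpoint is transfusion before catheterization, recorded around the procedure. The analysis is by intention to treat, with multiple imputation if needed, so few patients should be lost for this endpoint. If all 55 per group count, power is 0.783 by the plan's formula, and the exact likelihood-ratio test passes 0.80. This stands as a qualification: the true gap may be nearer 2 points than 5. It does not rescue the statement, because the plan itself reserves those 4 patients per group for loss, and the Wald, chi-square and Fisher tests stay below 0.80 even at 55.

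A second objection is that the hypothesis is worded as thromboelastometry and/or restrictive. Power could then mean the chance of showing at least one difference from control. With 90/65/65, a shared control group and chi-square tests at 0.0167, simulation puts that at about 0.90 with 51 per group. But the article's calculation is for a single pair and is then inflated for three pairwise tests, so it is power per comparison. If both differences from control are required, power is only about 0.64.

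A third objection is that the 20% is taken from a cited paper that is not at hand. Whether that paper gives 20% for two or for three comparisons cannot be checked. The finding does not depend on it: with the plan's own inputs, 20% does not give 0.80 at α 0.0167.

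Finally, type I error is not affected, and confidence intervals will show the imprecision of a null result. Both points are true. They limit the harm but do not make the power statement correct.

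**Conclusion.** The concern holds. The inflation in Sample size calculation and the significance level in Statistical analysis plan contradict each other. At α 0.0167, power for each comparison with control is about 0.75 with 51 evaluable per group and about 0.78 with 55, against the stated 0.80. The inflation needed for three comparisons is about one third, not one fifth.

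This rests on the plan's assumed rates of 90% and 65%, on the pooled formula that reproduces 43, and on Bonferroni at 0.0167 for each pair. It takes no account of the two Lan-DeMets interim analyses described under Data collection, monitoring and interim analysis. These are not in the sample size calculation and could lower power slightly further. The figures do not apply to Thromboelastometry-based v Restrictive, where the assumed rates are equal (65% each) and no power is planned.

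The shortfall is modest and does not undermine the trial, but the power stated for the primary efficacy endpoint is wrong and should be corrected.

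**What to change.** Restate the figures in Sample size calculation and leave enrolment as it is. Suggested text:

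> *With 51 evaluable patients per group and a two-sided α of 0.0167 per comparison, power for each comparison with the Coagulogram-based group is about 0.75 for 90% v 65% (about 0.78 if all 55 per group are evaluable), before allowing for interim analyses. Power of 0.80 is available for a reduction of about 27 percentage points.*

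Correct the justification of the 20% as well: an increase of that size corresponds to two comparisons (43 to 52 per group), while three at α 0.0167 need about one third more (42.6 to 57.0 by formula, 43 to 58 after rounding up).

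The cost is wording only. The stated power becomes slightly less favourable. No patients are added, and α, the tests and the endpoint do not change. If the sponsor prefers to keep 0.80 as the design power, the alternative is about 58 evaluable per group, or about 65 per group (195 in total) with 10% loss (58 / 0.90 = 64.4). That is a much larger change for a trial already recruiting, and correcting the statement does not require it.

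### The loss allowance is described as 10% added to the adjusted sample size, but the 4 patients per group are 7.8% of 51 and cover a loss of at most 7.3%

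*Protocol article*

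**What the plan says.** The section *Sample size calculation* of the protocol article sizes the trial on the primary efficacy endpoint, the proportion of patients transfused before central venous catheterization. The inputs are: "We assumed a transfusion rate of 90% in the Coagulogram-based group", "an absolute risk reduction of 25% for the Thromboelastometry-based and Restrictive groups" and "Using a study power of 0.80 and alpha of 0.05". These lead to 43 per group.

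Two increments follow. The first is 20%, printed as 8 per group, for the three pairwise comparisons. The second is the loss allowance: "To account for loss to follow-up, we have added 10% (*n* = 4) more patients to the adjusted sample size". The section concludes: "The final required sample will be 55 patients per group (total estimated sample size of 165 patients".

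The section *Statistical analysis plan* adds that "Two-tailed tests will be used" and that, for the three pairwise comparisons, "the α level will be adjusted to 0.0167". Allocation is equal across the three groups. No other section gives a different loss rate or explains which number the 10% is taken from.

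**The concern.** The sentence gives a percentage (10%), the number to which the increment is added (the adjusted size, 51) and a count (4). On the natural reading these three do not fit together, because 4 is not 10% of 51. The count decides the final number, so 55 per group carries a smaller allowance than the text says.

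The total of 165 is the number that recruitment works towards, and the two interim looks, at 55 and 110 patients, are thirds of it. A reader who relies on the 10% would believe that 51 evaluable patients per group are protected at that loss, and they are not.

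**Working it through.** **Inputs.** From *Sample size calculation*: 90% in the control group, 65% in each other group (90% minus 25 points), power 0.80, alpha 0.05, increments of 20% (8) and 10% (4). From *Statistical analysis plan*: two-sided tests, and 0.0167 for pairwise comparisons. From the section on randomization: a 1:1:1 ratio.

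**1. Reproduce the starting figure.** Pooled two-proportion formula without continuity correction, with mean proportion (0.90 + 0.65)/2 = 0.775:

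n = [1.960 × √(2 × 0.775 × 0.225) + 0.842 × √(0.90 × 0.10 + 0.65 × 0.35)]² / 0.25² = 42.6, so **43 per group**. This matches the protocol.

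**2. Reproduce the final figure.** 43 + 8 + 4 = **55 per group**, and 3 × 55 = 165. The printed counts add up.

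**3. Check each count against its percentage.**
- 20% of 43 = 8.6, printed as 8. The adjusted size is then 43 + 8 = 51.
- 10% of 51 = 5.1, printed as 4. In fact 4/51 = 7.8%.
- 10% of 43 = 4.3, which rounds down to 4. The unadjusted 43 therefore appears to be the base that was used.

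**4. What a 10% allowance on 51 would give.**
- Simple addition: 51 × 1.10 = 56.1, so 56 or 57 per group (168 to 171 in total).
- Keeping 51 after a 10% loss: 51/0.90 = 56.7, so 57 per group (171 in total).

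**5. What 55 per group covers.**
- Largest loss that still leaves 51: 4/55 = 7.3%.
- Evaluable at 10% loss: 55 × 0.90 = 49.5, so 49 to 50.

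**6. Effect on power.** Same formula, 90% versus 65%, two-sided:

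| Evaluable per group | alpha 0.05 | alpha 0.0167 |
|---|---|---|
| 49 | 85.4% | 72.5% |
| 49.5 | 85.7% | 73.0% |
| 50 | 86.1% | 73.5% |
| 51 | 86.7% | 74.5% |
| 55 | 89.2% | 78.3% |

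Going from 51 to 49.5 costs 74.5 − 73.0 = 1.5 points at 0.0167, and 86.7 − 85.7 = 1.0 point at 0.05.

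**The case against.** **The base may have been meant as 43.** The sentence can be read as adding 10% of the starting number on top of the adjusted one. Both increments then agree with their percentages apart from rounding down (8.6 to 8, 4.3 to 4), and the fault is an unclear base. This reading is fair and probably explains where the 4 came from. It does not rescue the allowance: 55 still fails to protect 51 against a 10% loss.

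**57 is not the protocol's own method.** The text speaks of adding 10%, which gives 56.1. Dividing by 0.90 is sound practice, but the document does not say that it was done. On the stated method the gap is about one patient per group. This stands, so the shortfall is best given as 1 to 2.

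**A 10% loss is unlikely for this endpoint.** Randomization follows consent and blood sampling, and the outcome is transfusion before the catheter goes in, so it is known soon afterwards. Analysis is by intention to treat, with multiple imputation when necessary. Withdrawal, or deferred consent that is not confirmed, could remove a few patients, but nothing in the document points to 10% for this endpoint. This stands and is the main reason why the point is small. It also makes the stated rationale for the allowance harder to follow.

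**A reader might infer that the trial misses its stated power.** The document does not support that. The only power it states is 0.80 at alpha 0.05, attached to 43 per group, and 49 to 50 evaluable still give 85.4% to 86.1% at that alpha.

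**Conclusion.** The sentence is wrong as printed, or at best leaves the base of the 10% unclear. On either reading 55 per group does not deliver a 10% loss allowance on 51; it allows for 7.3%. The gap is 1 to 2 patients per group (3 to 6 in total) and, if 10% really were lost, about 1.5 points of power at 0.0167. These power figures rest on the protocol's 90% and 65% and on the pooled formula that reproduces its 43.

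It would go too far to attribute the power deficit at 0.0167 to this slip. At that level power is already 74.5% with 51 evaluable and 78.3% with all 55, and the same formula needs 58 evaluable per group for 80%. That deficit comes mainly from the 20% multiplicity step, which is a separate point.

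This is a minor correction to a stated figure. It does not call for a larger trial: the interim looks at 55 and 110 fit 165, and four patients a month for 42 months gives 168.

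**What to change.** Keep 165 and change one sentence, in either of two ways:

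- State that 4 patients per group were added to 51, which allows for about 7% loss, and that at 10% loss 49 to 50 per group would be evaluable.
- State that no material loss is expected for the primary efficacy endpoint because it is observed before catheterization, and give the power for 55 evaluable per group at the alpha actually used (about 78% at 0.0167).

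The cost is one reworded sentence and a less favourable printed figure. It needs no additional patients, no change to the interim looks and no change to the analysis.
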